#### Withdrawal criteria

The patient will be withdrawn from the study if the clinician finds that the patient is in need of, or better served with other treatment, or if Exclusion criteria are met. The patient will also be withdrawn from the study if the clinical condition gets significantly worse according to the clinicians' judgement or if patients withdraw their consent. The date and the reason for discontinuation are noted. All patients prematurely discontinuing the trial must be seen for a final evaluation.

### Inclusion, randomization and masking of study groups

All patients suffering from a major depressive episode admitted to one of the nine study centres are evaluated for inclusion. During the screening the local participating psychiatrist will determine whether the patient fulfils the inclusion criteria and none of the exclusion criteria. Patients will be randomly assigned to the two groups. The randomization is stratified separately in each study centre. The patient and treating psychiatrist are unmasked about treatment modality. The assessments of depressive symptoms before and after ECT will be audio-taped. The audio-tapes will be co-rated by trained study personnel who are not involved in the treatment of the study patients. The analyses will be preformed on audio taped scores. There might be some patients who do not accept audio taping, in these cases investigator-rating will be used. Neuropsychological assessment is performed by trained test assistants who are blinded about treatment modality.

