### Efficacy

#### Primary response variable

Patients will be interviewed at start (visit 2), weekly on week 1-5 (visit 3-7), on week 6/endpoint (visit 8), on a follow-up-visit after 26 weeks (visit 9) and in case of depressive, manic or mixed symptoms at weeks 26 on a control-visit between 26-52 weeks (visit 10). Visit 10 should be performed in euthymic state if possible. Patients will be interviewed using MADRS. The primary response variable is change in total MADRS-score at endpoint versus baseline.

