### Methodological weaknesses

The use and policy regarding ECT differs between countries and hospitals. Thus there are no published guidelines defining objective clinical criteria for indications of treatment with ECT in bipolar depressions. In the present protocol "indication for ECT" is one of the inclusion criteria. This means that treatment with ECT would have been probable according to hospital practice regardless of the present study.

The assessments are performed by specially trained research staff which is not blinded for grouping of the patients. Most of the patients are acutely admitted to psychiatric acute wards due to the extensive symptom pressure.

The multicentre site design has potential problems regarding assessments and inter-rater reliability. However, multicentre design is a necessity in order to include sufficient number of patients in a reasonable time span. All raters and participants in the study have taken part in mutual training-sessions in the different assessments and rating scales. All participants have taken part in interrater-scorings. The scorings for the different study centres and the different participants are satisfactory.

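### Masking of the primary endpoint to treatment arm is not secured: the audio-tape raters need only be trained and uninvolved in treatment

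*Protocol article*

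**What the plan says.** The primary endpoint is a clinician-rated scale: "The primary response variable is change in total MADRS-score at endpoint versus baseline" (Primary response variable).

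The section Inclusion, randomization and masking of study groups describes an open comparison: "The patient and treating psychiatrist are unmasked about treatment modality". Its safeguard is tape rating. On what is taped it says: "The assessments of depressive symptoms before and after ECT will be audio-taped". On who rates: "The audio-tapes will be co-rated by trained study personnel who are not involved in the treatment of the study patients". On which scores count: "The analyses will be preformed on audio taped scores". On patients who refuse: "There might be some patients who do not accept audio taping, in these cases investigator-rating will be used". It then says of the cognitive tests: "Neuropsychological assessment is performed by trained test assistants who are blinded about treatment modality".

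Table 4 marks the MADRS as audio-taped at visits 2 and 8, without limiting this to one arm. The MADRS at weeks 1 to 5 is not marked as taped.

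Methodological weaknesses adds: "The assessments are performed by specially trained research staff which is not blinded for grouping of the patients".

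**The concern.** In a comparison of ECT with drug treatment the patient and the treating psychiatrist must know the allocation, so protection against rater expectation depends on who scores the tape and what that person knows. The article's condition concerns the rater's role in treatment, not the rater's knowledge of allocation. A member of the study team at the same hospital could meet it in full and still know which arm the patient is in.

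The expectation that could enter the scores is recorded in the Abstract, which describes ECT as generally regarded as the most effective treatment. If raters who know the arm share that view, part of the MADRS contrast could reflect rating and not patients. No later analysis can separate the two once the scores exist.

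**Working it through.** **Step 1. The plan's own figure.** A-priori power calculations gives a difference of 4 points, SD of change 7, two-sided α = 0.05, power 0.90 and a total of 132. The allocation ratio is not stated; 1:1 is assumed here.
- Normal approximation: n per arm = 2 × 7² × (1.960 + 1.282)² / 4² = 64.4, rounded up to 65, so 130 in total.
- Exact two-sample t-test: 130.7 in total, so 66 per arm and 132 overall, with power 0.903.

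The stated 132 reproduces. The sample size is not at issue.

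**Step 2. What is required of each assessor.**

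| Assessor | Stated condition | Feeds the primary endpoint? |
|---|---|---|
| Tape rater | Trained, not involved in treatment | Yes |
| Investigator, if taping is refused | None on masking | Yes |
| Research staff doing the assessments | Described as not blinded | Through the interview, and possibly through LOCF |
| Neuropsychological tester | Blinded to treatment | No |

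The explicit term is used for a secondary domain and not for the primary one.

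**Step 3. Can the tape reveal the arm?** The patient knows the allocation and the research staff are described as unblinded. Randomisation comes before wash-out (Method of assigning patients to treatment groups/Randomization), and baseline is visit 2, at the start of treatment (Statistical analysis). Both taped interviews therefore take place after allocation, and either could mention treatment.

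**Step 4. Knowledge of arm versus knowledge of visit.** A rater who knows only the visit may expect improvement in both arms alike, and this largely cancels in the between-arm comparison. Knowledge of arm is what biases the primary test.

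**Step 5. Illustrative size.** SE of the difference = 7 × √(2/66) = 1.22 points. With no true effect and an average between-arm rating shift b, the two-sided rejection probability is 1 − Φ(1.96 − b/SE) + Φ(−1.96 − b/SE).

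| Assumed b (points) | Share of the 4-point target | Rejection rate |
|---|---|---|
| 0 | 0% | 5% |
| 0.5 | 12.5% | about 7% |
| 1 | 25% | about 13% |
| 2 | 50% | about 38% |

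Every value of b is an assumption. The documents give none.

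**Step 6. Primary scores that do not come from tape.** Patients who refuse taping are scored by the investigator. Early leavers are handled by LOCF (Statistical analysis), which may carry forward a week 1 to 5 rating not marked as taped. Withdrawal criteria requires a final evaluation for early leavers but does not say whether it is taped.

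**Step 7. What is taped.** Read literally, taping before and after ECT covers only the ECT arm. ECT may also end before week 6 on remission (Study design), so the interview after ECT need not be visit 8. Table 4 has visits 2 and 8 with no restriction by arm. The two places need to be reconciled.

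**The case against.** **The text is silent, and silence is not unmasking.** A reader might infer that the blind cannot hold. The article does not support this. It nowhere says that tape raters know the arm, it makes no express claim of a blind for the MADRS, and masked rating of tapes from open interviews can reduce bias. This part of the objection stands: masking is not secured, which is less than saying it must fail.

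**The weaknesses section may not mean the tape raters.** A reader might also take its statement about unblinded staff to cover every assessor. That reading would contradict the blinded neuropsychological testers, so the statement cannot be literal for all. It fits the on-site interviewers at least as well, and it is an open disclosure of a limitation. This stands too. Disclosure does not, however, settle what the tape raters may know.

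**A journal article leaves operating detail to the full protocol.** This is fair for tape coding or interview scripts taken alone. It does not answer the main point: the article states the condition on tape raters, and that condition is weaker than the one it states for the cognitive testers.

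**The illustrative error rates would fit any trial with unmasked rating at this SD and size.** True. They show what is at stake and do not measure a bias in this trial.

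**The taping phrase is only loose wording.** Probably so, since Table 4 does restrict the MMS to the ECT group and does not restrict taping. It is still easily corrected.

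**Conclusion.** The point holds in a limited form. The analysed MADRS scores come mainly from raters who are required to be trained and uninvolved in treatment, but not masked to arm. Masking of the primary endpoint is therefore not secured, and arm-related expectation could bias the contrast. The documents do not show that tape raters are unmasked or that masking is bound to fail.

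The size is unknown. With 1:1 allocation, SD 7 and 66 per arm, assumed shifts of 1 and 2 points would give false-positive rates of about 13% and 38%. Investigator ratings for patients who refuse taping, and possibly untaped scores carried forward, are further routes for unmasked ratings into the primary analysis.

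**What to change.** **In Inclusion, randomization and masking of study groups:**
- State that the planned tape raters are masked to treatment arm, score coded tapes from visits 2 and 8 of both arms pooled in random order, and do not rate patients from their own centre.
- Have the interviewer ask the patient at the start not to mention treatment.
- Have each rater record a guess of arm, and report the guesses.
- Describe taping as taking place at visits 2 and 8 in both arms, to agree with Table 4.

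**In Methodological weaknesses:** make clear that the unblinded staff are the on-site interviewers.

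**In Statistical analysis:** add a sensitivity analysis limited to tape-rated scores, because investigator ratings and possibly untaped LOCF scores also enter the primary analysis.

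**Cost.** The changes need a coding list, a random rating order, a short interview instruction and one extra item on the rating form, with the raters already planned. Up to 132 × 2 = 264 tapes would be rated in batches and moved between centres, which delays scoring and needs secure handling. Having a third person cut disclosures from the tapes is not proposed: it needs extra staff and could remove content that bears on the depression score. The sample size stays at 132. Because tapes can be kept, coded re-rating by masked raters remains possible after enrolment has begun.

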#### Statistical analysis

Response and remission rates will be compared using Chi Square tests. Secondary outcomes and cognitive function will be analysed with multiple regression analyses and other suitable statistical methods. ANOVAs and t-test will be made on a LOCF basis. Categorical variables will be analysed using chi square tests. Ordinal variables will be analysed using non-parametric tests in addition to using T tests and ANOVA. Time to remission and/or response will be analysed using survival analysis. The statistical analysis will be done by the scientific research team with assistance from experts in statistics. All patients who receive at least one medication with study medicine or ECT will be included in the analysis of the safety, demographic and baseline characteristic data. An analysis of treatment-emergent adverse events will be performed. All subjects who receive at least one medication with study medicine and provide post - baseline efficacy measurements will be included in efficacy data analyses (intention to treat). We will use last observations carried forward for subjects who leave the study prematurely. Analyses only including patients fulfilling the treatment will also be done. Baseline for all analyses is visit 2 (start of drug or ECT treatment).

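### Analyses are to use audio-taped scores, but MADRS is taped only at visits 2 and 8, so last observation carried forward from visits 3 to 7 puts unblinded, mixed-rater change scores into the primary test

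*Protocol article*

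**What the plan says.** Patients and treating psychiatrists know the allocation. For the depression ratings, the section Inclusion, randomization and masking of study groups sets up a second rating from tape:

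- What is recorded: "The assessments of depressive symptoms before and after ECT will be audio-taped"
- Who rates the recordings: "The audio-tapes will be co-rated by trained study personnel who are not involved in the treatment of the study patients"
- Which scores count: "The analyses will be preformed on audio taped scores"
- One exception: "There might be some patients who do not accept audio taping, in these cases investigator-rating will be used"

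In Table 4 (Assessments), the footnote for audio taping is attached to the MADRS and IDS entries at visit 2 (week 0) and visit 8 (week 6). The weekly entries at visits 3 to 7 do not carry it.

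The Statistical analysis section takes visit 2 as baseline and limits the efficacy set to treated patients with a post-baseline efficacy measurement. On early leavers it says: "We will use last observations carried forward for subjects who leave the study prematurely". Under Withdrawal criteria: "All patients prematurely discontinuing the trial must be seen for a final evaluation". Under Methodological weaknesses, on the live ratings: "The assessments are performed by specially trained research staff which is not blinded for grouping of the patients".

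The primary variable is the change in total MADRS from baseline to endpoint. The section Primary response variable labels visit 8 as week 6/endpoint.

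**The concern.** Three rules meet at the primary endpoint and do not fit together. The analysis is to rest on taped scores. Tapes are scheduled only at the two ends of the six weeks. A patient who leaves in between is to be analysed on the last value observed. If that value comes from visits 3 to 7, no tape of it exists, and the exception to the taped-score rule covers refusers, not leavers.

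Two things are at stake. First, in an open trial, rating from tape by people outside the treatment team is the only stated safeguard for the depression scores, and no tape is scheduled for a patient between visits 2 and 8. Leaving is unlikely to be random: withdrawal turns on the judgement of clinicians who know the allocation, patient or clinician may choose treatment outside the study, and ECT has to be indicated for every patient, including those allocated to drugs. Leaving may therefore differ by arm and be related to outcome, although the article gives no expected rates.

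Second, subtracting a taped baseline from a live site rating gives a difference between two raters as well as between two times.

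**Working it through.** **The plan's own figure.** Inputs from A-priori power calculations: difference 4, SD of change 7, two-sided alpha 0.05, power 0.90. I assume 1:1 allocation.

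- Normal approximation: n per arm = 2 × (1.960 + 1.282)² × 7² / 4² = 64.4, so 65 per arm and 130 in total.
- Exact t-test: 65 per arm gives power 0.8985 and 66 per arm gives 0.903, so 132 in total.

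The stated 132 reproduces. This point does not affect it.

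**The rules applied to each kind of patient.**

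| Patient | Baseline (visit 2) | Endpoint value under the stated rules |
|---|---|---|
| Completes, accepts taping | taped | taped (visit 8) |
| Refuses taping | investigator rating | investigator rating, by stated exception |
| Leaves early, last observation at visits 3–7 | normally taped | untaped site rating, not blinded |
| Leaves early, seen at a final evaluation | normally taped | not stated whether taped |
| Leaves with no post-baseline rating | normally taped | outside the efficacy set |

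The third row cannot satisfy both the taped-score rule and last observation carried forward. The fourth row decides how many patients fall into the third, and the article leaves it open.

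**Illustrative size.** The documents give neither the share of untaped endpoints nor any rater shift, so both are assumptions. Let f be the share of endpoints that are untaped (the same in both arms) and b the shift in the arm contrast, in MADRS points, that unblinded rating adds to those endpoints. The spurious difference in means is f × b. With 66 per arm and SD 7, the standard error of the difference is 7 × √(2/66) = 1.22. The last column is the two-sided rejection rate when there is no true effect.

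| f | b | f × b | As share of the 4-point target | Rejection rate (nominal 5%) |
|---|---|---|---|---|
| 10% | 2 | 0.2 | 5% | 5.3% |
| 10% | 4 | 0.4 | 10% | 6.2% |
| 20% | 2 | 0.4 | 10% | 6.2% |
| 20% | 4 | 0.8 | 20% | 10.0% |
| 30% | 2 | 0.6 | 15% | 7.8% |
| 30% | 4 | 1.2 | 30% | 16.5% |

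**Mixed raters.** A constant offset between tape raters and site raters cancels between arms only if the same share of each arm has a mixed change score. Assuming a 3-point offset and 25% versus 10% early leavers, the contribution is (0.25 − 0.10) × 3 = 0.45 points. Its sign is unknown, so it could add to the shift above or offset it.

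**The case against.** The strongest reply is that the final evaluation may well be taped. Every patient who discontinues must have one, and visit 8, a taped visit, carries the label endpoint, so it could be read as the endpoint visit whenever it occurs. The text neither says nor excludes this. A reader might infer that every early leaver enters with an unblinded score. That goes too far: a taped final evaluation would prevent it, and leavers with no post-baseline rating are not in the efficacy set. What stands is narrower: any leaver whose last observation is an untaped visit.

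Other readings are also possible for such a patient: exclusion for want of a taped post-baseline score, site ratings at both ends as for refusers, or the taped baseline carried forward. That several are open shows the rules need reconciling.

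A reader might also count the refusers as a contradiction. They are not: the fallback is an openly stated exception, it depends on the patient's consent, and refusers plausibly have the same source at both ends. It is a disclosed limitation.

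The wording that assessments before and after ECT are taped might suggest taping in the ECT arm only. Table 4 does not support that: the taping footnote has no arm restriction, whereas the MMS footnote does.

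Nor should taped be equated with blinded. The tape raters are described only as outside the treatment; the neuropsychological testers, by contrast, are called blinded. Whether tape raters are masked to arm is not stated, and the product f × b measures only what untaped ratings add beyond taped ones.

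Every input to the illustration is assumed, and the reported rater training with satisfactory inter-rater scorings argues against a large constant offset. That is fair, but it does not address raters' knowledge of the arm.

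Finally, an article may leave such detail to the full protocol or analysis plan. Here, though, the stated rules conflict, and an evaluation that was never recorded cannot be recovered by a later analysis plan.

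**Conclusion.** The point holds in limited form. The taped-score rule, the taping schedule and last observation carried forward conflict for early leavers whose last post-baseline rating is from visits 3 to 7. As written, they enter the primary test with an unblinded site rating against a normally taped baseline.

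The bias cannot be computed from the documents. Under the assumed ranges (10 to 30% untaped endpoints, 2 to 4 points of shift) it is 0.2 to 1.2 points against the 4-point target: negligible at the low end and material at the high end. Both inputs are my assumptions, as is 1:1 allocation in the rejection rates.

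Response and remission inherit the same mixture of sources. A reader might infer that time to response or remission rests wholly on unblinded ratings. Visit 8 is taped, so this is true only of events timed before week 6. This is a cheap improvement to the primary endpoint, worth making before further data are collected; it does not show that the primary result would be invalid.

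**What to change.** 1. State that the final evaluation of a patient who discontinues is audio-taped and is treated as the endpoint assessment.
2. Where no taped endpoint exists, use the site rating at both baseline and endpoint, so that each change score has one rating source. A live visit 2 rating should exist, since the tapes are described as co-rated. This removes the offset between raters but not the effect of knowing the arm.
3. Give tape raters recordings coded without arm or visit, and say so. Coding cannot remove what a patient says on the tape.
4. Report a sensitivity analysis limited to patients with taped scores at both ends, beside the main analysis and not in place of it, because these patients are a selected subset.
5. Label response or remission timed before week 6 as based on unblinded ratings.

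Replacing refusers' observed scores by imputing taped ones is not recommended: it discards observed data, and refusers have no taped baseline from which to impute. Whether last observation carried forward should itself be replaced is a separate question; these changes settle only the source of the rating.

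The cost is a short amendment and one extra recording and rating per early leaver, by personnel already in place. A patient who refuses taping or does not attend the final evaluation will still lack a taped endpoint.

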### Description of treatment

#### Method of assigning patients to treatment groups/Randomization

Patients' eligibility will be established before randomization to one of the treatment options. Relevant patients with BD are addressed in order to establish whether they are willing to be screened for the study. The patients must be assigned a patient number and sign the consent form after receiving oral and written information about the study prior to undergoing any study procedures. Patients will be randomized strictly sequentially, as patients are eligible for randomization. If a patient discontinues from the study, the patient number will not be reused, and the patient will not be allowed to re-enter the study.

We perform a stratified randomization separately for each centre using the default random number generator of SPSS 15 with a random seed. The randomization lists are kept concealed from the investigators.

After randomization patients will enter a wash out phase if necessary. The recommended time for patients to be without concomitant medication in contradiction to the study protocol is 5 t 1/2 for patients randomized to ECT and a varying time for patients randomized to treatment as usual.

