#### Inclusion and exclusion criteria

The inclusion criteria were designed to ensure that the included patients are typical for patients referred to ECT in Norway in order to have results that are clinically significant, while the exclusion criteria are designed to ensure the patients' safety. Inclusion and exclusion criteria are shown in table 1 and 2.

**Table 1 T1:** Inclusion criteria

Diagnosis of DSM-IV-TR [52] of Bipolar I or Bipolar II disorder as verified by the semi-structured diagnostic interviews SCID [37] or MINI plus [36]. The diagnosis may be supported by information from significant others, and from hospital records. Angst's hypomania checklist [53] is used to increase the detection of hypomanic symptoms. SCID or MINI plus will be used to diagnose the patient.
ECT is indicated.
Severity: meet DSM-IV-TR criteria of depressive episode, MADRS [40] of 25 or above
Treatment resistance: None response to two trials (during lifetime) with mood stabilizers with proven efficacy in bipolar depression (lithium, lamotrigine, quetiapine, olanzapine) and/or antidepressants.
A trial is defined as at least 6 weeks in adequate or tolerated dose as reported by the patient, or patients that have been unable to comply with 6 weeks trials of mood stabilizer or an antidepressant.
None response: Less than 50% reduction in MADRS values or still meet DSM -IV-TR criteria of depressive episode
Inpatients the first week after start of treatment condition
The patients are to be treated by the psychiatrist at the hospital for the whole duration of the study (6 weeks)
Age ≥ 18
Patient competent to give informed consent according to the judgement of the clinician
Written informed consent
Patient sufficiently fluent in Norwegian language to ensure valid responses to psychometric testing (for patients enrolled to neuropsychological assessment: Norwegian as primary language or 12 years attendance of a Norwegian school)

**Table 2 T2:** Exclusion Criteria

Earlier ECT none response
ECT within the last six months
Rapid cycling BD (e.g.4 or more episodes per year)
Use of medication or substances (such as pethidine, alcohol, drugs) incompatible with treatment (medication or ECT). Such medication must be stopped a least 5 half-lives before start of treatment.

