##### Wash out Phase

The recommended time for patients to be without concomitant medication in contradiction to the study protocol is 5 t 1/2 for patients randomized to ECT and a varying time for patients randomized to treatment as usual.

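### The efficacy set called intention to treat leaves out randomised patients lost in the arm-specific wash-out before treatment starts; analyse all randomised patients in their assigned arm

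*Protocol article*

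**What the plan says.** All references are to the protocol article.

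- **Timing.** Under Method of assigning patients to treatment groups/Randomization: "After randomization patients will enter a wash out phase if necessary".
- **Length.** The same section recommends "5 t 1/2 for patients randomized to ECT and a varying time for patients randomized to treatment as usual". The section Wash out Phase repeats this.
- **Masking.** Inclusion, randomization and masking of study groups says that neither the patient nor the treating psychiatrist is masked. The randomisation lists themselves are concealed from investigators.
- **Withdrawal.** Under Withdrawal criteria a patient is "withdrawn from the study if the clinical condition gets significantly worse" in the clinician's judgement, or when the clinician finds the patient "better served with other treatment, or if Exclusion criteria are met". Date and reason are recorded, and everyone who discontinues early is to have a final evaluation.
- **Efficacy set.** Statistical analysis requires at least one administration of study treatment and adds that those who also "provide post - baseline efficacy measurements will be included in efficacy data analyses (intention to treat".
- **Baseline.** The same section: "Baseline for all analyses is visit 2 (start of drug or ECT treatment". Last observation carried forward is used for early leavers. The only other set it names for analysis of outcome, patients who complete treatment, is narrower.
- **Size.** Trial sample and recruiting centres plans 132 patients, and A-priori power calculations needs 132 in the analysis.

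**The concern.** An intention-to-treat comparison is protected by randomisation because nothing that happens after allocation decides who is analysed. Here something does. Between allocation and visit 2 lies a phase whose demands depend on the arm, supervised by clinicians who know the arm and have discretion to withdraw patients. These are severely ill patients, some of them coming off medication, so worsening in this interval is plausible.

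If losses differ between arms in number or in kind, the groups compared at week 6 are no longer the groups that were randomised. The label would lead readers of the results to assume that they are.

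**Working it through.** **1. Does any rule keep a patient who is lost in wash-out?** Set the rules side by side for a patient randomised, not yet treated, and withdrawn before visit 2.

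| Rule | Result for this patient |
|---|---|
| Received study treatment | No |
| Has a visit 2 baseline | No, visit 2 is the start of treatment |
| Has a post-baseline efficacy score | No, there is no baseline to follow |
| Last observation carried forward | Nothing after baseline to carry |
| Final evaluation at discontinuation | The patient is seen, but still fails the treatment condition |
| Analysis of treatment completers | Excluded |

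No rule returns the patient to an efficacy analysis.

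**2. The plan's own sample size.** Inputs from A-priori power calculations: difference 4, SD of change 7, two-sided α = 0.05, power 0.90. Allocation of 1:1 is assumed, since the article states no ratio. The two-sample t-test needs 65.33 per arm, so 66 per arm and 132 in total. This reproduces the stated figure. Power is 0.903 at 66 per arm and 0.899 at 65 per arm. There is no allowance for losses, but a few cost little power. The issue is bias.

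**3. Possible bias (assumed inputs).** The article gives no loss rate, so take k of 66 patients lost in one arm and none in the other, with the lost patients' mean MADRS change worse than that of the retained patients by a gap of 3.5, 7 or 10.5 points (0.5, 1 or 1.5 SD).

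Shift in the arm mean = (k/66) × gap. For k = 7 and gap 7: 7/66 × 7 = 0.742 points, and 0.742/4 = 18.6% of the 4-point target. The false-positive rate is the two-sided rejection probability of the t-test with 66 against 66 − k patients, SD 7, no true difference, and this shift.

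| k lost | Shift in points (gap 3.5 / 7 / 10.5) | % of 4 points | False-positive rate |
|---|---|---|---|
| 1 | 0.053 / 0.106 / 0.159 | 1.3 / 2.7 / 4.0 | 0.0502 / 0.0508 / 0.0519 |
| 3 | 0.159 / 0.318 / 0.477 | 4.0 / 8.0 / 11.9 | 0.0519 / 0.0575 / 0.0671 |
| 7 | 0.371 / 0.742 / 1.114 | 9.3 / 18.6 / 27.8 | 0.0599 / 0.0904 / 0.1426 |

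Equal losses of patients with the same prognosis in both arms give no bias, only lower power (0.870 at 10% in each arm).

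**4. Would ordinary imputation repair it?** Take k = 7 and gap 7, and impute the lost patients by regression on baseline fitted to the treated patients of the same arm. In simulation the bias was 0.74 points with this imputation and 0.74 without it. The model fills in the outcomes of treated patients, which is the very assumption in doubt.

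**5. Cost of analysing everyone (assumed inputs).**
- If k of 66 ECT patients get no ECT benefit, the difference becomes 4 × (1 − k/66): 3.94, 3.82 and 3.58 for k = 1, 3 and 7. Power at 66 per arm is 0.894, 0.875 and 0.830.
- If 7 patients in each arm effectively switch treatment, the difference is 4 × (1 − 14/66) = 3.15 and power about 0.73.

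**The case against.** The strongest reply is that this is a conventional modified intention-to-treat set with its definition printed beside the label, and that exposure is small. Wash-out happens only where needed, eligibility is settled and the control drug chosen before randomisation, and patients at high suicidal risk or unable to comply are already excluded. No passage reports a loss in wash-out, and early leavers do get a final evaluation. The larger error rates need about 10% of one arm lost, none of the other, and a large gap in prognosis.

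Most of this stands as a limit on size. It does not restore the lost patients. Requiring a first treatment does least harm when masking makes loss before treatment unrelated to arm. Here the arm is known and the phase before treatment differs by arm.

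Four stronger readings are tempting and are not supported:

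- **That allocation could be foreseen.** The lists are concealed, and the arm becomes known only after assignment.
- **That the result will favour one arm.** The article gives no direction.
- **That unequal wash-out is itself an error.** Permitted drugs differ by arm, so some difference is inherent.
- **That incomplete wash-out forces withdrawal, or that the half-life rules contradict each other.** No passage describes a check that wash-out is complete. Table 2 says "Such medication must be stopped a least 5 half-lives before start of treatment" while Wash out Phase speaks of a recommended time, but the two rules overlap only in part, and control-arm intervals may be in Additional file 1, which is not shown.

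**Conclusion.** The point holds in a limited form. Followed as written, the plan removes from the primary comparison any randomised patient lost before visit 2, through a phase that differs by arm and decisions made with knowledge of the arm, and it calls the remainder intention to treat. Because the article fixes the set, the label and the baseline outright, this is not a detail left to a later document.

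The size cannot be derived from the article. With 1:1 allocation and one-sided losses assumed, one to three losses per 66 are nearly harmless (false-positive rate at most 0.067). Losses of about 10% of one arm with a clearly different prognosis would matter (up to 0.143 at a gap of 1.5 SD). The change is worth making because it is cheap, not because serious bias has been shown.

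**What to change.** 1. **Statistical analysis.** Make the primary efficacy analysis include all randomised patients in their assigned arm. Where visit 2 did not take place, use the visit 1 MADRS that Table 4 already schedules as baseline.
2. **Withdrawal criteria.** Extend the final evaluation already required: unless consent is withdrawn, a patient who stops before or during treatment may have other care but is still asked for the week 6 MADRS.
3. **Missing week 6 scores.** Do not impute never-treated patients from treated patients in the same arm under missing-at-random alone. Use an assumption that gives them no benefit of the assigned treatment, such as reference-based or delta-adjusted imputation, and vary it in sensitivity analyses.
4. **Reporting.** Give losses before treatment by arm. Keep the treated, post-baseline set as a sensitivity analysis, labelled modified intention to treat.

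The cost is wording in two sections, one extra contact for patients who stop early, and some dilution. ECT is indicated for every patient at entry, so a control patient withdrawn in wash-out may receive it off-study and still count as a control. That is why the power of about 0.73 for seven switches per arm belongs beside the 0.83 for seven untreated ECT patients. Using the visit 1 score also mixes a few baselines from before wash-out with the rest, and Table 4 marks audio-taping only at visit 2 and week 6, so those few scores would be investigator-rated.
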